##### Analyses of secondary outcomes

The LRFS, MFS, OS, and CSS will be analyzed using the same analytic methods as described for the primary outcome above. In addition, Gray’s test will be used to compare cumulative incidence curves for cancer-specific death if competing risks exist. For group comparison in the postoperative complication rate, the chi-square test or Fisher’s exact test will be used as appropriate.

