However, anesthetic medication types may have disparate effects on cancer recurrence (Melamed et al. 2003). Preclinical and biomarker studies have shown that volatile anesthetics might promote immunosuppression and create a pro-malignant environment including upregulation of hypoxia-inducible factor that supports cancer cell proliferation, migration, and angiogenesis, whereas propofol may preserve cell-mediated immunity and inhibit tumor angiogenesis (Buckley et al. 2014; Cho et al. 2017; Hiller et al. 2018a; Hiller et al. 2018a; Iwasaki et al. 2016; Jaura et al. 2014; Kim and Reviews 2017; Looney et al. 2010; Markovic-Bozic et al. 2016; Melamed et al. 2003; Tavare et al. 2012; Wall et al. 2019).

Despite the availability of biologically plausible explanations, clinical evidence that propofol-based total intravenous anesthesia (TIVA) can reduce tumor recurrence after curative resection remains inconsistent (Chang et al. 2021; Enlund et al. 2022; Hasselager et al. 2021; Hovaguimian et al. 2021; Jun et al. 2017; Lai et al. 2019; Lee et al. 2016; Makito et al. 2020; Wigmore and Farquhar-Smith 2016; Yoo et al. 2019; Yoon et al. 2022; Zheng et al. 2018), mainly because previously conducted studies have been retrospective or observational in nature. Given the risk of residual confounding inherent in observational studies, randomized trials are required to evaluate the influence of anesthetics on oncologic outcomes.

In this multinational, multicenter clinical trial, we will test the hypothesis that local or metastatic recurrence after curative resection of NSCLC is lower in patients randomized to propofol-based total intravenous anesthesia (TIVA group) than in patients randomized to volatile anesthesia (GAS group). Secondary hypotheses are that overall survival (OS) is increased when patients receive TIVA rather than GAS anesthesia and that postoperative complication rates are not different between the TIVA and GAS anesthesia groups.

In this report, we outline our approach and study protocol to establish an a priori record of the proposed study methods and endpoints.

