### Outcomes

#### Primary and secondary outcomes

The primary outcome of this study is recurrence-free survival (RFS) after curative resection of NSCLC. The observed time-to-recurrence is defined as the duration from the date of surgery to the earliest date between the recurrence/metastasis date and the last follow-up date due to death from any cause, any uncontrollable factor during the study, or the end of the study.

Secondary survival outcomes are locoregional RFS (LRFS), metastasis-free survival (MFS), overall survival (OS), and cancer-specific survival (CSS). The observed time-to-events for LRFS and MFS are defined similarly to that of RFS. The observed time-to-event for OS is defined as the duration from the date of surgery to the earliest date among the date of all-cause death and the last follow-up date due to any uncontrollable factor during the study, or the end of the study. The observed time-to-event for CSS is defined as the duration from the date of surgery to the earliest date among the date of cancer-specific death, and the last follow-up date due to death from any cause other than cancer-specific death, any uncontrollable factor during the study, or the end of the study. Other secondary outcomes are postoperative complications. The postoperative complication is a composite outcome defined as any complication occurring within 7 days post-surgery or at discharge if earlier. The applicable complications are defined by the Society of Thoracic Surgeons (STS) general thoracic surgery databases (Crabtree et al. 2018), and the Clavien-Dindo classification (Wong, Oliver, and Moonesinghe 2017). The postoperative complication is a reasonable surrogate for an immediate postoperative outcome, which we believe will be similar between study groups based on Pasin et al.’s meta-analysis of short-term mortality after propofol vs. volatile anesthesia (95 studies, *n* = 9806 total patients) (Pasin et al. 2015).

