### Statistics

#### Sample-size calculations

Sample size was calculated based on RFS, the primary outcome of the trial. We expect an overall 3-year recurrence rate of 20% in GAS group based on previous studies (Taylor et al. 2012) [*N* = 1143, event rate of 10%, 20%, and 35% for Stage I, II, III, respectively] and Yun et al. (Yun et al. 2022) [*N* = 6012, event rate of 13%, 35%, and 60% for Stage I, II, III, respectively]). A Cox regression on the anesthesia group (TIVA group versus GAS group) with a sample size of 4845 observations achieves 80% power at a 0.05 significance level to detect a hazard ratio of 0.83 in the TIVA group compared to the GAS group. This HR corresponds to an absolute risk reduction of 3% in the TIVA group compared to the GAS group. Since the most important predictors of NSCLC survival are patient-related factors and aggravating tumor characteristics (Enlund et al. 2023), we expect only a 3% difference related to the anesthetic regimens. Although a 3% absolute difference between study groups is small, we believe it is clinically significant given the ease and low cost of the anesthetic interventions. Anticipating a 10% dropout rate, 5384 subjects should be enrolled to obtain a final sample size of 4845 subjects (in each group, 2692 subjects) (Table 2). No adjustment is made on other covariates in Cox regression, under the assumption that there is no collinearity between the anesthesia group and covariates. As no study has yet examined the effect of the TIVA group compared to the GAS group on RFS, we assumed a conservative condition for the correlation structure which leads to maximizing the estimated sample size. Although we will be conducting competitive enrollment, we expect a total of 5384 subjects to be enrolled in SMC:SNU: Other in a ratio of 4:3:3 (SMC; Samsung Medical Center, SNU; Seoul National University).

**Table 2 Tab2:** The estimated study power using two-sided log-rank tests at a significance level of 0.05 according to different assumed 3-year RFS rates at each arm

Scenario	Hazard ratio	1/hazard ratio	Risk reduction	*N*	*N***	*N* per group			
						Total	SMC	SNU	Others
1	0.65	1.54	5%	1132	1260	630	315	126	63
2	0.73	1.37	5%	1533	1704	852	427	170	85
3	0.78	1.29	5%	2010	2236	1118	559	224	111
4	0.81	1.24	5%	2374	2640	1320	660	264	132
5	0.83	1.2	2%	6460	7180	3590	1796	718	358
6	0.83	1.2	3%	4845	5384	2692	1348	538	268
7	0.83	1.2	4%	3876	4307	2154	1078	430	214
8	0.83	1.2	4%	3230	3592	1796	898	360	178

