##### Other details for analyses

All baseline variables will be descriptively compared between two intervention groups using appropriate summary statistics, such as mean and standard deviation, median and quartiles, or frequency and percent, and also proper testing methods, including two-sample *t*-test or Mann–Whitney test, chi-square test, and Fisher’s exact test. All tests will be two-tailed, and the statistical significance will be declared if *p* value < 0.05. All data analyses will be performed by a statistics analytic team using SPSS software (version 27.0; IBM Corp., Armonk, NY, USA) or R software (version 4.2.2; R Foundation for Statistical Computing, Vienna, Austria) or SAS software (version 9.4; SAS Institute, Cary, NC, USA) according to a pre-established statistical analysis plan.

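### Complication rates are hypothesised not to differ between arms, but the only planned analysis is a test of difference, which cannot support that hypothesis

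*Protocol article*

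**What the plan says.** The last part of the Background lists the secondary hypotheses. One is that overall survival is better with TIVA. The other is that "postoperative complication rates are not different between the TIVA and GAS anesthesia groups".

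Primary and secondary outcomes defines the complication outcome as a binary composite: "The postoperative complication is a composite outcome defined as any complication occurring within 7 days post-surgery or at discharge if earlier". It adds, citing a meta-analysis of short-term mortality, that this is an outcome "which we believe will be similar between study groups".

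Analyses of secondary outcomes gives the method in one sentence: "For group comparison in the postoperative complication rate, the chi-square test" or, where appropriate, Fisher's exact test. Other details for analyses sets the general rule: "All tests will be two-tailed, and the statistical significance will be declared if" the p value is below 0.05.

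The article states no margin, interval criterion, expected rate or power for complications. The sample size was set for recurrence-free survival alone.

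**The concern.** The hypothesis and its test point in opposite directions. A chi-square or Fisher test asks whether the data contradict equal rates. If p is above 0.05, equality has not been ruled out, but neither has a difference that matters. If p is below 0.05, the stated hypothesis is rejected even if the gap is too small to matter. Neither result can establish that the rates are similar.

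The article says it sets down methods and endpoints in advance. An analysis plan that follows it carries the mismatch forward, and one that adds a margin goes beyond the published record. At stake is whether the trial can report, alongside any effect on recurrence, that early complications were alike under the two techniques.

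**Working it through.** **Inputs from the document.** Evaluable sample 4845 (Sample-size calculations); allocation 1:1 (Randomization), so n = 4845/2 = 2422.5 per arm; two-sided alpha 0.05 (Other details for analyses).

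**Assumed inputs.** Complication rates of 15, 20, 30 and 40%; illustrative margins of 3 and 5 points. The document gives neither. The 3-point value is borrowed from the absolute difference in recurrence that the article regards as clinically significant. The article does not apply it to complications.

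**The plan's own figure.** The plan says a Cox regression "with a sample size of 4845 observations achieves 80% power at a 0.05 significance level to detect a hazard ratio of 0.83".
- Events by Schoenfeld's formula: 4(1.960 + 0.842)² / (ln 0.83)² = 905.
- Mean event rate from 20% in GAS and 17% in TIVA: 18.5%.
- 905/0.185 = 4892, against 4845 stated, a gap of 1.0%.
- With 10% dropout: 4845/0.9 = 5383.3, rounded up to 5384, as stated.

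The primary sample size therefore reproduces. It says nothing about complications, so 4845 is used below only as the number available.

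**Step 1: precision.** With the same rate p in both arms, SE = √[2p(1 − p)/n], and the 95% half-width is 1.96 × SE. At p = 0.30: SE = √(0.42/2422.5) = 0.01317, half-width 0.0258.

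**Step 2: chance that a real 3-point difference is non-significant.** With p in the lower-rate arm and q = p + 0.03 in the other, SE₁ = √{[p(1 − p) + q(1 − q)]/n}, and P(non-significant) ≈ 1 − Φ(0.03/SE₁ − 1.96). At p = 0.30: SE₁ = √[(0.2100 + 0.2211)/2422.5] = 0.01334; 0.03/0.01334 = 2.249; 1 − Φ(0.289) = 0.39.

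**Step 3: power to place the whole 95% interval inside ±m when the true difference is zero.** Power = 2Φ(m/SE − 1.96) − 1. At p = 0.30:
- m = 0.05: 2Φ(3.797 − 1.96) − 1 = 0.93.
- m = 0.03: 2Φ(2.278 − 1.96) − 1 = 0.25.

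| Assumed rate | 95% half-width (points) | True 3-point difference non-significant | Power, 5-point margin | Power, 3-point margin |
|---|---|---|---|---|
| 15% | 2.0 | 20% | 99.6% | 67% |
| 20% | 2.3 | 28% | 98% | 48% |
| 30% | 2.6 | 39% | 93% | 25% |
| 40% | 2.8 | 44% | 89% | 14% |

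A true 2-point difference would be non-significant in about 52, 60, 67 and 71% of trials at the same four rates.

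**Sensitivity to the interval rule.** Two one-sided tests at 5%, equivalent to a 90% interval, are less strict. For a 3-point margin at a 30% rate they raise power only from 25% to 47%.

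**The case against.** The strongest reply is that this is a condensed article about a secondary outcome. It refers to a separate analysis plan that is not shown, and a margin or interval may be set there. Similarity is also worded in the outcomes section as a belief drawn from earlier evidence. Part of this stands: the absence of a margin from the article is not in itself a fault. But the article does fix both a hypothesis and a test, and the two do not match. That does not depend on the unseen plan.

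Four stronger readings are tempting, and the document does not support them.

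- **That a non-significant p-value will be reported as proof of similarity.** No sentence says so. It is an inference, although it is the only way the planned test could appear to confirm the hypothesis.
- **That this is the trial's main safety statement.** The article lists complications among its other secondary outcomes. Its separate section on safety outcomes does not mention them, and its concluding claims concern recurrence.
- **That ending the count at discharge biases the comparison.** The window is "any complication occurring within 7 days post-surgery or at discharge if earlier", so it does depend on length of stay. But the article gives no length of stay and no sign that it will differ by arm, and patients, surgeons and outcome assessors are blinded. The chart review described under Measurements also ends at the earlier of day 7 and discharge, so counting to day 7 for everyone would need follow-up that is not planned.
- **That the unadjusted test is invalid.** It is a valid test of difference. The fault is that it answers a different question from the one posed.

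**Conclusion.** The mismatch is real and is confined to one secondary hypothesis. The planned test can refute the statement that complication rates do not differ but cannot support it. At assumed rates of 15 to 40%, a true 3-point difference would go undetected in roughly a fifth to over two fifths of trials, so a non-significant result would not be evidence of similarity.

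The sample is large enough for an informative interval, about ±2 to ±3 points. Whether it is large enough for an equivalence claim depends on the margin: at a 5-point margin power is 89% or more across these rates, while at 3 points it is 67% at best. These figures rest on assumed rates and margins, 2422.5 patients per arm and the normal approximation. The mismatch itself rests only on the text and is certain. It should be corrected, but it does not touch the primary analysis.

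**What to change.** Make the risk difference with its 95% confidence interval the main result for postoperative complications. The chi-square or Fisher test may stay as a supporting result. Then take one of two routes and state it in the Background and in Analyses of secondary outcomes.

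- **(a) Equivalence.** The steering committee fixes and justifies a margin before any outcome data are seen. No difference is claimed only if the whole 95% interval lies inside the margin.
- **(b) Estimation.** Reword the secondary hypothesis as an aim to estimate the difference in complication rates, with no claim that the rates do not differ.

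Route (b) costs a change of wording. Route (a) costs wording and one decision on the margin, and its feasibility depends on that decision. With the planned sample it works for a margin near 5 points but is underpowered near 3 points, in which case (b) is the realistic choice. Neither route changes the endpoint, its observation window or the data collected.

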##### Other details for analyses

All baseline variables will be descriptively compared between two intervention groups using appropriate summary statistics, such as mean and standard deviation, median and quartiles, or frequency and percent, and also proper testing methods, including two-sample *t*-test or Mann–Whitney test, chi-square test, and Fisher’s exact test. All tests will be two-tailed, and the statistical significance will be declared if *p* value < 0.05. All data analyses will be performed by a statistics analytic team using SPSS software (version 27.0; IBM Corp., Armonk, NY, USA) or R software (version 4.2.2; R Foundation for Statistical Computing, Vienna, Austria) or SAS software (version 9.4; SAS Institute, Cary, NC, USA) according to a pre-established statistical analysis plan.

## Discussion

Preclinical studies have demonstrated that volatile anesthetics might promote immunosuppression and the development of a pro-malignant environment that supports cancer cell proliferation, migration, and angiogenesis, while propofol preserves cell-mediated immunity and inhibits tumor angiogenesis (Hiller et al. 2018a; Kim and Reviews 2017; Wall et al. 2019).

Despite these biological explanations, clinical evidence that propofol-based TIVA might reduce tumor recurrence and metastasis after curative resection remains uncertain and inconsistent (Chang et al. 2021; Enlund et al. 2022; Enlund et al. 2023; Hasselager et al. 2021; Hovaguimian et al. 2021; Jun et al. 2017; Lai et al. 2019; Lee et al. 2016; Makito et al. 2020; Wigmore et al. 2016; Yoo et al. 2019; Yoon et al. 2022; Zheng et al. 2018), mainly because previous studies have been conducted as retrospective or observational studies..

Recently, a multicenter randomized controlled trial was published on this subject (the Cancer and Anesthesia Study; CAN NCT01975064). Elund et al. (2023) compared sevoflurane and propofol for 5-year OS in breast cancer (*n* = 1670). The numbers who survived at least five years were 773/841 [91.9% (95% CI 90.1–93.8)] in the propofol group and 764/829 [92.2% (90.3–94.0)] in the sevoflurane group [HR 1.03 (0.73–1.44); *P* = 0.875]. Thus, TIVA did not increase OS compared to sevoflurane anesthesia. Instead, increasing age, BMI, ASA classification, and number of comorbidities were associated with the OS together with polypharmacy, smoking, no alcohol use, and more severe oncological characteristics.

Sessler et al. (2019) compared regional (paravertebral block with propofol sedation) vs. general anesthesia (sevoflurane) (*n* = 2132) in patients with breast cancer. Regional anesthesia with propofol sedation did not reduce breast cancer recurrence after potentially curative surgery when compared with general anesthesia with sevoflurane in a median 3-year follow-up [hazard ratio 0.97, 95% CI 0·74–1·28; *p* = 0·84]. The study design permitted supplemental low-dose sevoflurane in the regional group potentially obscuring differences between Propofol and sevoflurane-based anesthetics.

Both previous studies had event rates (OS or RFS) of only 10%; given the relatively large expected differences in outcomes related to the anesthetic regimens ((a 5% difference in OS (Enlund et al. 2023) and a 30% reduction in cancer recurrence (Sessler et al. 2019) in a total of 1670 and 2132 patients, respectively), statistical power may have been inadequate.

Additionally, results of randomized controlled trials conducted for breast cancer may not relate to NSCLC. The potential of anesthetic drugs to modify tumor biology, including local recurrence and metastasis, may differ substantially between cancer types (Tsuchiya et al. 2003). Breast cancer resection procedures tend to be relatively short and commensurately lower exposure to anesthetic drugs. Furthermore, the superficial location of these tumors may facilitate easier surgical management with a lower risk of cancer cell dissemination. Given the substantial evidence for anesthetic influence on cancer recurrence and host immunosuppression, there is a clear need for additional trials to evaluate the potential benefits of propofol-based TIVA in patients undergoing major surgery. Furthermore, evidence-based medicine requires at least two well-conducted randomized trials to influence guidelines.

Currently, one multicenter study in progress is comparing TIVA versus volatile agents for a variety of major cancer surgeries (lobectomy or pneumonectomy, esophagectomy, radical cystectomy, pancreatectomy, partial hepatectomy, hyperthermic intraperitoneal chemotherapy, gastrectomy, cholecystectomy or bile duct resection, *n* = 1804) with the primary outcome of all-cause mortality (ongoing, NCT03034096). The aforementioned CAN trial includes another arm which includes patients undergoing primary resection of colorectal cancer and is also under progress (Enlund et al. 2019). Another upcoming Volatile Anesthesia and Perioperative Outcomes Related to Cancer trial (VAPOR-C trial), is scheduled to be completed in 2025 in patients with lung or colorectal adenocarcinoma. This trial is a 2 × 2 factorial design comparing propofol versus sevoflurane general anesthesia, with or without intravenous (IV) lidocaine (NCT04316013).

A potential weakness of our study is that it is a pragmatic protocol, meaning that all other aspects of anesthesia, besides the choice of anesthetic, may vary among participating sites. However, the pragmatic nature of the protocol also has the potential to increase the external validity and generalizability.

Confirmation of the study hypothesis would demonstrate that a relatively minor and low-cost alteration in anesthetic management has the potential to reduce cancer recurrence risk in NSCLC, an ultimately fatal complication. In addition, implementation would be easily accomplished since TIVA is a routinely used modality familiar to anesthesiologists. Rejection of the hypothesis would end the ongoing debate about the relationship between cancer recurrence and anesthetic management.

## Data Availability

Data sharing including the full protocol, individual participants, and other relevant study data will be considered upon reasonable request. Only with the permission of the Data Review Board of Samsung Medical Center, the anonymized data will be available from the principal investigator ([name]).

## Abbreviations

AJCC: The American Joint Committee on Cancer
AMC: Asan Medical Center
ASA: American Society of Anesthesiologists
CONSORT: A Consolidated Standards of Reporting Trials
CRF: Case report form
DMP: Data management plan
ECOG: The Eastern Cooperative Oncology Group
eCRF: Electronic case report form
GAS: Inhalational gas anesthesia
GCP: Good Clinical Practice
NSCLC: Non-small cell lung cancer
OS: Overall survival
PBW: Predicted body weight
PEEP: Positive end-expiratory pressure
RFS: Recurrence-free survival
SMC: Samsung Medical Center
SNU: Seoul National University
STS: The Society of Thoracic Surgeons
TIVA: Propofol-based total intravenous anesthesia
TNM: Tumor, node, metastasis
TV: Tidal volume
